### Data analysis

#### Understanding what works and at what cost

Documentary evidence will inform the evaluation in terms of development and progress of the reconfigurations, e.g. providing detail on chronology, responsibilities and time dedicated to governing the change process
[31,32].

The documentary analysis will establish the models applied in both reconfigurations. It will also provide information on key processes (e.g. governance activities, consultation events and designation of services). It will also contribute to understanding of the cost of change (by examining the work and time dedicated to governance, development, and implementation of the changes).

#### Analysis of process and outcome data

Routinely collected data will be analysed for two purposes. First, to analyse outcomes, econometric and cost effectiveness analyses will be conducted. Second, there will be an analysis of whether the reconfigurations are associated with significant changes in how services were provided, i.e. an analysis of process measures.

### Analysis of outcomes

#### Econometric analysis

The outcome variables measured at the Trust level in each time period will be regressed against the covariates, with particular interest in interactions showing the impact of region following the introduction of stroke service reconfigurations. The regression model is:

$$y_{\mathrm{it}}=\alpha_{0}+\alpha_{1}A_{i}+\alpha_{2}Y_{t}+\alpha_{3}R_{\mathrm{it}}+\alpha_{4}X_{\mathrm{it}}+e_{\mathrm{it}}$$

where *y* is the outcome of interest (mortality, LOS), *i* indicates Trust, *t* indicates year, *A* is region, *Y* is year, *R* is an indicator variable taking the value one if stroke services in Trust *i* in each region *A* in year *t* have been reconfigured (1 = yes, 0 otherwise), *X* is a set of patient and Trust characteristics, the αs are coefficients to be estimated, and *e* is an error term. The regression model used will depend on the nature of the dependent variable. Of particular interest are the sign and statistical significance of the coefficient α_*3*_. If for reconfigurations in London or Greater Manchester α_*3*_ indicates a favourable result, i.e. a reduction in mortality and/or on LOS, the following cost-effectiveness analysis will be undertaken.

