### The reconfigurations

While there were numerous parallels between the London and Greater Manchester reconfigurations, there were also important differences.

Both reconfigurations were supported by local commissioners and received additional finance to support the changes. However, the London reconfiguration received significantly more resource per head of population: the London resource (£20 million) represented £2.42 per head of population (8.28 million
[14]), and £1,816.13 per estimated annual stroke admission, whereas the Greater Manchester resource (£3.5 million) represented £1.56 per head of population (2.24 million
[14]), and £1,174.81 per estimated annual stroke admission (Note estimates for stroke admission are derived from a peer-reviewed analysis of the South London Stroke Register
[15]).

Both reconfigurations went through similar processes, including consultation, data analysis, model development, and specification and selection of services. However, approaches to leadership and governance of these processes differed: the changes in Manchester were led by the Greater Manchester and Cheshire Cardiac and Stroke Network (which facilitates stakeholder collaboration to improve commissioning and provision of stroke and cardiac care across the Greater Manchester area), whereas in London they were led by Healthcare for London, a programme within the city’s Strategic Health Authority (the organisation responsible for managing all NHS commissioning and provider organisations within London). Therefore, the London reconfiguration was led by a body with greater executive authority. The proposed changes in London and Manchester both met with a degree of resistance, for example, from local communities, service providers, and public representatives. The ways in which this was managed by reconfiguration leaders had a significant influence on how the models developed.

In terms of the models applied, prior to reconfiguration, in both London and Greater Manchester, patients presenting with stroke were taken to the nearest accident and emergency (A&E) department to receive stroke care. Both of the reconfigurations aimed to concentrate specialist stroke services in ‘hub and spoke’ models of provision. However, there were significant differences in these models, in terms of the services provided by the different levels of the new systems and the criteria applied in deciding where patients should be treated in the two systems.

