In the reconfigured London model (Figure 1A), the local population is served by eight Hyperacute Stroke Units (HASUs), which provide immediate response to stroke, including assessment, stabilisation and any primary intervention; 24 Stroke Units, offering rehabilitation services; and 24 Transient Ischaemic Attack (TIA) services. Any person presenting with a suspected stroke is transferred to a HASU for assessment and treatment, then repatriated to a Stroke Unit, to a nursing home, or to their own home. In creating this system, a number of healthcare organisations lost either some or all of their stroke services (e.g. closure of stroke unit).

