**Figure 1 F1:**
[figure not shown]
Simplified post-reconfiguration models in Greater Manchester and London.

In the reconfigured Greater Manchester model (Figure 1B), the local population is served by 10 hospital organisations, or ‘trusts,’ providing District Stroke Centre (DSC) services; one Trust also hosts a Comprehensive Stroke Centre (CSC), which offers hyperacute stroke services in a neurosciences centre with access to interventional neuro-radiology and neurosurgery (24 hours per day, seven days per week); and two Trusts host Primary Stroke Centres (PSCs), providing thrombolysis (from 7 am to 7 pm, Monday to Friday). Any individual presenting within four hours of developing stroke symptoms is transferred to either the CSC or PSC for hyperacute care; once stable, he/she is repatriated either to a DSC, to a nursing home, or their own home. If presenting outside this four-hour ‘window,’ stroke patients in Greater Manchester are taken to the DSC to which they are nearest, much as they did prior to reconfiguration.

While there have been reconfigurations of acute services over recent years
[16,17], there have been few similar examples within the NHS of services being completely restructured for such large populations over such a short period of time; and nowhere else in the world has attempted anything similar for stroke.

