### Data collection

#### Understanding what works and at what cost

To establish what models were applied and how they were developed and put into action in London and Greater Manchester, the evaluation will analyse a range of documentary evidence. This will include project board papers, service designation criteria, and tariff documentation.

Using routinely collected data, the evaluation will assess whether the reconfigurations were associated with changes in process, outcomes, and costs of care. Data will be collected retrospectively from 2004, up to the point at which services began to change; while ‘after’ data will be collected from the points at which the new models were fully in place, through to December 2013.

Care process measures have been selected for the evidence indicating relevance to quality of care and their positive association with improved outcomes
[28-30]. Measures include proportion of patients appropriately receiving thrombolysis, admitted to a stroke unit for 50% of their stay, appropriately receiving aspirin in the acute period, assessed by a multidisciplinary team, and receiving a swallowing test within the first 24 hours of care. These data will be drawn from national data sources (the Royal College of Physicians’ Sentinel Stroke Audit, the Stroke Improvement National Audit Programme (SINAP), and the Sentinel Stroke National Audit Programme (SSNAP)).

Outcome measures will include patient’s length of hospital stay, discharge destination, readmission rates, and mortality (in hospital, at 30 days, and at one year); these data will be drawn from HES and ONS datasets. Patient’s independent function (measured through Barthel Index score at discharge, and/or Modified Rankin score) will be drawn from Sentinel audit data, SINAP and SSNAP.

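### Outcomes and exposure are both defined by Trust although the reconfigurations move patients between Trusts, so α3 can reflect patient routing rather than care

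*Protocol article*

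**What the plan says.** The Econometric analysis section sets the unit: "The outcome variables measured at the Trust level in each time period will be regressed against the covariates". In the equation, i is Trust and t is year. R equals one when stroke services in that Trust and year have been reconfigured. The other terms are region, year, and a set X of patient and Trust characteristics that is not listed. The outcomes named for the model are mortality and length of stay. A favourable α3 on either one leads to the cost-effectiveness analysis.

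The Data collection section lists length of stay and discharge destination, followed by "readmission rates, and mortality (in hospital, at 30 days, and at one year); these data will be drawn from HES and ONS datasets".

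The account of the reconfigurations describes the patient flows:

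- Before, in both regions: "patients presenting with stroke were taken to the nearest accident and emergency (A&E) department to receive stroke care".
- After, London: "Any person presenting with a suspected stroke is transferred to a HASU for assessment and treatment, then repatriated to a Stroke Unit", or to a nursing home or home. There are eight hyperacute units and 24 Stroke Units. Some organisations lost part or all of their stroke services.
- After, Greater Manchester: "Any individual presenting within four hours of developing stroke symptoms is transferred to either the CSC or PSC for hyperacute care"; then "once stable, he/she is repatriated either to a DSC, to a nursing home, or their own home". Later presenters go straight to the nearest District Stroke Centre (DSC).

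**The concern.** The intervention changes the population of the unit on which it is measured. There are three routes by which this can reach α3.

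- **Split stays.** A patient who moves from a hub to a unit in another Trust may generate two Trust spells where there was one before.
- **Changing panel.** London Trusts that lose all stroke services may drop out after the change. The equation carries a region term and no Trust term, so a change in which Trusts contribute can move the London mean.
- **Re-sorting.** In Greater Manchester the four-hour rule sends early and late presenters to different Trusts. Hub and DSC Trusts then differ in patient mix by design.

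All three begin with reconfiguration and occur only in the reconfigured regions, so region and year effects do not absorb them. The transferred share may also differ between regions, because all suspected strokes in London enter the hub pathway but only early presenters do in Greater Manchester. The direct London versus Greater Manchester comparison (research question 5) is exposed for that reason.

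What is at stake is the two-step plan. A fall in length of stay alone is enough to start the economic analysis, and splitting stays produces such a fall.

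**Working it through.** The article gives no length of stay, mortality rate, transfer share or effect size, so there is no figure to reproduce. Every input below is assumed, except the counts of units and Trusts.

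**1. Counts from the article.** London has 24 Stroke Units and 8 hyperacute units, so at least 16 of 24 (67%) Stroke Units are not at a hub. Greater Manchester has 10 Trusts. Reading the one comprehensive and two primary centre Trusts as among the ten, 7 of 10 are not hubs.

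**2. Split stays, no care effect.** Let a share p of patients have two Trust spells, with total stay L and in-hospital death risk m unchanged. Spells per patient are 1+p, so the means per spell are L/(1+p) and m/(1+p). With L = 20 days and m = 20%:

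| p | Days per spell | In-hospital deaths per spell | Fall |
|---|---|---|---|
| 0.2 | 16.7 | 16.7% | 17% |
| 0.4 | 14.3 | 14.3% | 29% |
| 0.6 | 12.5 | 12.5% | 38% |

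The proportional fall does not depend on L or m.

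**3. The article's regression under no care effect.** This simulation used region, year and R, without X. Assumptions: 24 reconfigured and 120 control Trusts, 10 years with R = 1 in the last four, 400 patients per Trust-year, exponential stays with mean 20 days, 20% in-hospital mortality, and unweighted Trust means. In the reconfigured region all patients enter one of 8 hubs. After 3 days, those still in hospital whose home Trust is one of the other 16 move there.

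- Unlinked spells: mean α3 over 25 runs was -3.8 days and -3.8 percentage points (single-run standard errors about 1.1 days and 1.2 points).
- Linked stays assigned to the first Trust: -0.04 days and -0.07 points.
- Linked stays assigned to the home Trust: -0.02 days and +0.12 points.

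A hand check of the unlinked result: the transferred share is (16/24) × exp(-3/20) = 0.574. The hub mean is 20/3 + (2/3) × 20 × (1 - exp(-3/20)) = 8.5 days. The other Trusts stay at 20 days, because an exponential stay has the same expected remainder at any time. The unweighted mean is (8 × 8.5 + 16 × 20)/24 = 16.2 days, a fall of 3.8. Weighting by spells without linking would give 20/1.574 = 12.7 days, a larger fall.

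**4. Re-sorting with linked stays, Greater Manchester.** Assume ten equal catchments of one unit each, a share s = 0.5 presenting within the window and spread evenly over three hubs, and each stay assigned to the first Trust. Risk is 25% for early and 15% for late presenters, so the overall risk before is 20.0%.

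- Volume per hub: 0.5 + 10 × 0.5/3 = 2.167.
- Hub risk: (0.5 × 0.15 + 1.667 × 0.25)/2.167 = 22.7%.
- DSC-only risk: 15%.
- Unweighted Trust mean: (3 × 22.7 + 7 × 15)/10 = 17.3%.
- Patient-weighted mean: (3 × 2.167 × 22.7 + 7 × 0.5 × 15)/10 = 20.0%.

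With the two risks reversed, the unweighted mean rises to 22.7%. With equal risks it does not move.

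**The case against.** The strongest reply is that a Trust-year mean is only a level of aggregation. The article does not say that each Trust's part of a stay counts as a separate admission. It lists the patient's length of hospital stay as the outcome, and following deaths to 30 days and one year already requires patient-level records. Linked stays fit the text equally well, and with them the simulated α3 is close to zero. Rules for joining spells, assigning transferred patients and weighting may sit in the full protocol or analysis plan. This stands: a reader might infer that the plan counts unlinked spells, or that the outcomes must change mechanically, and the article supports neither.

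Other stronger readings also fail:

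- The article does not say that Trust means are equally weighted, nor that no stay was split before the change.
- X may capture some of the difference in mix.
- Readmission is neither named in the model nor part of the trigger. Counting transfers as readmissions would make reconfiguration look worse, so it could not start the economic analysis.
- Mortality at 30 days and one year is not diluted by discharge to another Trust as in-hospital mortality is, although double counting and Trust assignment still matter.
- Transfers within one Trust, to a nursing home or to home create no second Trust spell.
- A false favourable result would only start the cost-effectiveness analysis, which has its own endpoints.

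The reply does not remove the stated choice of Trust for both outcome and exposure. Step 4 shows that linkage alone does not settle that choice. The Discussion acknowledges possible bias from admitting less complex patients, but not transfers or routing.

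**Conclusion.** The point holds in conditional form. Outcome and exposure are tied to a unit whose patients the intervention redistributes, so α3 can mix routing with care.

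- If spells are not linked, length of stay and in-hospital mortality per spell fall by 17% to 38% for p between 0.2 and 0.6. This assumes no transfers before the change and every second spell counted as an admission. The direction favours starting the economic analysis.
- If stays are linked but Trust means are unweighted, the shift can go either way: from 20.0% to 17.3% or 22.7% in the assumed Greater Manchester example. It requires that risk differs by time of presentation and that X misses the difference.

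These percentages are not estimates of bias in this study, because the article supplies neither transfer shares nor risks. The case for change rests on the stated unit and the stated patient flows. A method without this weakness is available on data already planned.

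**What to change.** State the following before the outcome analysis:

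1. Link each patient's HES spells across Trusts into one stroke admission, counted once. Define length of stay and in-hospital death on that admission.
2. Fit the model to patient-level HES and ONS records with case-mix covariates. If Trust-period means are kept, weight them by number of patients; this does not replace step 1.
3. Assign patients to region of residence, with Trust of first arrival as a sensitivity analysis.
4. Set the reconfiguration indicator by region and admission date, keeping Greater Manchester's phased dates.

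The cost is linkage programming and a heavier analysis, on data sources the study already plans to use. Trust-specific effects would no longer be the main quantity.

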#### Research questions

1. What were the key processes of and factors influencing the development and implementation of two reconfigurations of acute stroke services?

2. To what extent have changes delivered process and outcome improvements?

3. Have changes delivered improvements that stakeholders (e.g. commissioners, staff, patients and the public, and reconfiguration leads) think are worthwhile?

4. Have changes delivered value for money?

5. Has the additional investment in London provided better outcomes than those achieved for less resource in Manchester?

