## Design/methods

### Design

#### Understanding what works and at what cost

Identifying what process and outcome changes have occurred, and at what cost, provides evidence about the extent to which the reconfigurations have succeeded in their objectives of changing the system of service provision and quality of care. This component of the evaluation will analyse documentary evidence to establish the models applied in London and Greater Manchester; it will also identify whether any changes in process and outcomes can be associated with these changes.

In assessing the nature and results of the two reconfigurations, the evaluation will apply a controlled before-and-after design
[24]. This will compare the London and Manchester models in terms of the impact they had on processes, outcomes, and costs of care. In addition to comparing London with Greater Manchester pre- and post-reconfiguration, the analysis will make a wider comparison with the rest of England. This approach will permit observed changes to be analysed in the context of changes that take place in the rest of England over this period. A two-step approach will be taken to the analysis of outcomes: in the first instance, the impact of the reconfigurations on mortality and length of stay will be investigated; if evidence of impact on these is found, a more detailed cost-effectiveness analysis will be undertaken.

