#### Analysis of process changes

To analyse process changes, the regression model described for the econometric analysis of impact on outcomes will be applied to process variables, covering the same ‘before’ and ‘after’ periods. This will allow an assessment of whether relative performance across London and Greater Manchester remains constant pre- and post-reconfiguration – i.e. whether the reconfigurations are associated with changes in processes of care. Extending the ‘location’ comparison to include the rest of the English NHS will permit these changes to be assessed in the context of any nationwide changes that may have taken place over the period analysed.

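### The outcome regression has one reconfiguration coefficient where its own text reads one per region, so as written it yields neither region's effect nor the London–Manchester contrast of research question 5

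*Protocol article*

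**What the plan says.** The Econometric analysis section regresses Trust-level outcomes on region A, year Y, a reconfiguration indicator R and covariates X. It introduces the model "with particular interest in interactions showing the impact of region following the introduction of stroke service reconfigurations". R "is an indicator variable taking the value one if stroke services in Trust" i, in each region A and year t, have been reconfigured, and is zero otherwise. The result is taken from one number: "Of particular interest are the sign and statistical significance of the coefficient" α3. The gate to the cost-effectiveness work then begins "If for reconfigurations in London or Greater Manchester" and continues with α3 pointing in a favourable direction.

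Three other places set what this model has to deliver:

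- Research question 5: "Has the additional investment in London provided better outcomes than those achieved for less resource in Manchester".
- The design section, on the controlled before-and-after comparison: "This will compare the London and Manchester models in terms of the impact they had on processes, outcomes, and costs of care".
- The section on the reconfigurations, on the two hub-and-spoke systems: "However, there were significant differences in these models".

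The same regression is reused for functional independence and for process measures. For the latter the protocol adds: "This will allow an assessment of whether relative performance across London and Greater Manchester remains constant pre- and post-reconfiguration", and treats this as equivalent to asking whether the reconfigurations are associated with process change. The next sentence extends the comparison to the rest of the English NHS.

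**The concern.** The paragraph does not agree with itself. It promises interactions by region and reads α3 for one region or the other, but the equation has one indicator and one coefficient, with no term that lets the effect of reconfiguration differ between London and Greater Manchester.

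An analyst who codes the equation as printed will get one blended effect of two systems that the protocol says differ in important ways. Three things then go wrong. Neither region's own effect is estimated. Research question 5 has no matching parameter. The cost-effectiveness gate, worded for one region or the other, is decided on a figure that belongs to neither. Because the equation is reused, the first two problems pass to the functional and process analyses.

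There is a smaller point in the process section. Both regions were reconfigured, so a stable relative position between them does not by itself show that reconfiguration had no association with care processes.

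**Working it through.** The protocol article gives no effect size, power or sample size for this analysis, so there is no figure to reproduce. The question is what α3 estimates.

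**Inputs from the protocol.** Data run from 2004 to December 2013 (Data collection). The London model is dated 2010 (Analysis of cost-effectiveness). Greater Manchester has 10 hospital trusts and London has 24 Stroke Units (The reconfigurations).

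**Assumptions.** The number of London Trusts is not stated; 24 (the Stroke Unit count as a stand-in) and 32 were tried. Rest-of-England Trusts: 60 or 110. London start: 2010 or 2011. Greater Manchester start: 2009 to 2011. The check is linear and noise-free, without X.

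**Step 1: what α3 is.** Write R = R_L + R_M, where R_L and R_M are the London and Greater Manchester parts, and let the true effects be δL and δM. Let R̃ be the residual of R after regression on region and year. Then

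α3 = Σ R̃·y / Σ R̃·R = wL·δL + wM·δM, with wL = Σ R̃·R_L / Σ R̃·R and wL + wM = 1.

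**Step 2: the weights.** With a common start year, wL is London's share of reconfigured Trusts. For 24 and 10 Trusts, wL = 24/34 = 0.706 and wM = 10/34 = 0.294. For 32 and 10, wL = 32/42 = 0.762. Different start years need the fitted regression:

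| London / Gtr Manchester / rest | Starts (London, Gtr Manchester) | wL | wM |
|---|---|---|---|
| 24 / 10 / 110 | 2010, 2010 | 0.706 | 0.294 |
| 32 / 10 / 110 | 2010, 2010 | 0.762 | 0.238 |
| 24 / 10 / 110 | 2010, 2009 | 0.691 | 0.309 |
| 24 / 10 / 110 | 2011, 2009 | 0.655 | 0.345 |
| 24 / 10 / 60 | 2010, 2011 | 0.730 | 0.270 |

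**Step 3: what is reported.** First row of the table, effects in arbitrary units with negative favourable:

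| True δL | True δM | α3 |
|---|---|---|
| −2 | 0 | 0.706 × (−2) = −1.41 |
| 0 | −2 | 0.294 × (−2) = −0.59 |
| −2 | −2 | −2.00 |
| −2 | +2 | −1.41 + 0.59 = −0.82 |

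A favourable α3 is compatible with benefit in both regions, in one only, or with harm in Greater Manchester.

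**Step 4: is the contrast elsewhere in the model?** No. α1 carries time-constant differences between regions and α2 carries changes common to all regions. No function of the printed coefficients equals δL − δM.

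**Step 5: the split model.** With R_L and R_M entered separately, the design has full rank (14 of 14 columns) and returns δL and δM exactly in every scenario above.

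**The case against.** The strongest reply is that this is compact notation rather than a wrong analysis. R is already a region-by-period product, since it is one only for Trusts in a reconfigured region after the change. Its definition refers to each region A, the lead-in mentions interactions, and the gate names London or Greater Manchester. A and X also stand for sets of terms under a single coefficient symbol, so α3 may too. Separate fits of each region against the rest of England may also have been meant.

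Much of this stands: region-specific effects were probably intended. It does not remove the inconsistency. The article chose to print the equation, describes R as one indicator and draws its conclusion from one coefficient. Nor does any reading of the notation name the contrast for research question 5.

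Some stronger inferences are not supported:

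- *Equal process improvement in both regions would be read as no change.* The comparison is extended to the rest of England, and under the printed regression equal effects of −2 return −2.00, not zero. Only the explanatory clause is loose.
- *A blended effect would feed the cost-effectiveness ratio.* The simulation is to be populated for London and Greater Manchester, before and after. Only the decision to proceed rests on α3.
- *London's weight is its share of stroke admissions.* The funding figures imply 20,000,000/1,816.13 = 11,012 and 3,500,000/1,174.81 = 2,979 admissions, or 79% London, but the plan states no admission weighting.
- *Research question 2 demands an effect for each region.* It asks only how far the changes delivered improvement. The need for separate effects comes from question 5, the design section and the gate.

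**Conclusion.** The Econometric analysis section contradicts itself, and the printed equation does not deliver what its own text and research question 5 require. Fitted as written, α3 averages the London and Greater Manchester effects and leaves the contrast undefined. This holds whatever the Trust numbers, provided both regions contribute years before and after the change and the rest of England serves as control.

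The size is only indicative. A London weight of about 0.7, ranging from 0.66 to 0.76, rests on assumed Trust counts and start years in a linear model without covariates. The effects of −2, 0 and +2 are inputs chosen to show the mechanism and say nothing about what happened in either region.

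A reader might infer that the study cannot estimate regional effects at all. That goes too far: the planned data and comparator support both effects and their difference once the model is written to match the stated intention.

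**What to change.** 1. Replace α3·R_it with α3L·(London×post)_it + α3M·(Manchester×post)_it, where post marks a Trust's reconfigured years, and name the rest of England as the comparator.
2. Report α3L and α3M for outcomes, functional independence and process measures.
3. Answer research question 5 from α3L − α3M with its confidence interval, not by noting which coefficient reaches significance. If separate fits per region are preferred, the interval must allow for the shared comparator.
4. State that the cost-effectiveness gate is applied to the region-specific coefficients.
5. In the section on process changes, reword the explanatory clause so that change in each region is judged against the rest of England, with the London–Manchester comparison as a further question.

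This takes one extra model term and a few sentences, and no new data. Each regional coefficient, and the contrast, will be less precise than the pooled coefficient.
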